***Nomothetic analysis***

The ideographic analysis described above will be complemented by nomothetic analyses, which will involve hierarchical linear modeling. Baseline demographic variables will be examined using multiple regression and discriminant function analysis to determine if there are predictors of response to treatment.

***Moderator analysis***

Depending on the characteristics of the sample that will be recruited, demographic and other variables can be explored to identify moderators and other predictors of the treatment response. Other than using the software of Lakens (2103) and Cumming (2102), analyses will be carried out using the Statistical Package for Social Science (SPSS), Excel, Jamovi, and Sigma Plot.

## Anticipated costs

*Participant reimbursement*: The costs of this study are being funded by the University of Canterbury (funds provided to PhD students) and the University of Canterbury Foundation. At the beginning of the study, participants will need to meet with the study coordinator at the Mental Health and Nutrition Research Lab, Te Puna Toiora, to sign the informed consent form and to discuss any questions or concerns they might have with regards to the study. If the participants cannot be met in person, the meeting will take place online (e.g. via Zoom). Further, they will need to meet the study coordinator (every four weeks to answer parent- and child-related questionnaires as well as to provide information on compliance and potential side-effects of the intervention. To cover their driving costs to university, the participants are compensated with a $10 petrol voucher every time they meet the study coordinator at the university.

If the participants do not live in central Christchurch, or in case of New Zealand moving up to alert level 2, 3, or 4, the Lightning Stiks will need to be couriered to the participants as a meeting in person will not be possible. As a consequence, a mail cost of $30 per participant is necessary, as each participant will receive five packages containing the Lightning StiksTM, costing $6 each.

## Resources

The product we are testing is provided free of charge by the manufacturer (True Hope). They do not provide any financial support and are not involved in the study in any other way.

## Timetable

| **Date** | **Event** |
| --- | --- |
| February 2022 | Recruitment starts |
| February 2023 | Recruitment ends |
| August 2023 | Data analysis starts |

**The timeline might change based on how quickly approval from the Human and Disability Ethics Committee is granted. The earliest point in time recruitment might start would be September 2021.

## Ethics

The overall safety of all involved in of the outmost importance. The following safety protocol outlines what safety measures have been put in place to ensure safety of researchers and participants at the University.

## Safety protocol related to visits at the University Lab:

The University of Canterbury has very clear Health and Safety procedures for all visitors. We have a dedicated Health and Safety Team at the University: <https://www.canterbury.ac.nz/about/health-and-safety/>. The Mental Health and Nutrition Lab, Te Puna Toiora, is situated within the extensive facilities of the School of Psychology, Speech and Hearing, closely adjacent to clinics for audiology, clinical psychology, and speech therapy. All students and staff are trained to deal with emergency situations, such as evacuations, fire, and earthquakes. The Director of the Te Puna Toiora Mental Health and Nutrition Lab is a First Aid Certificate holder and we are equipped with a First Aid Kit. All short-term visitors are briefed as to the Emergency evacuation procedures. All staff and students who work with individuals under the age of 18 obtain a police check. The Director of the lab ([name]), [name], a research investigator involved in this study, and one of the current PhD students are registered psychologists such that in the event of any concerns for the wellbeing of participants, we have on hand trained professionals capable of dealing with such circumstances that may arise. In addition, within 20 meters of the lab there are a further 6 university staff who are registered psychologists available for consultation should the need arise.

Participant safety is the most important concern. Every potential participant will be screened to ensure that there are no known physical/mental or metabolic (e.g. hemochromatosis – an inability to metabolise iron; Wilson’s disease – an inability to metabolize copper) conditions that may preclude participation. Safety of the intervention will be assessed once a month during the study period via a survey examining side effects and adverse events. When a serious adverse event is reported, it will be discussed with the study physician who will determine the appropriate course of action. In the case of worsening psychiatric symptoms or suicidal ideation with plan and intent, contact will be made with appropriate mental health services.

Research participants will be informed if any new information regarding the products' safety is brought to our attention during the trial. If we find that a child’s symptoms have increased to a clinically significant degree or that the product is causing any harm, we may discuss with the participant and their family the possibility of withdrawing them from the trial or may decide that they should discontinue their participation in the trial. Participants may be referred to their General Practitioner until the condition associated with an adverse event has resolved or until it is stable. All adverse events will be documented. Serious adverse events would include events that result in hospitalisation, life-threatening disability or death.

If a participant, for any reason, requires treatment with certain therapeutic agents (i.e. antibiotics), we will note what they are taking and for how long. If a protocol exclusion violation has occurred (i.e., participant requires psychiatric medications), the participant’s involvement will be discontinued. If any participant is discontinued from the trial or decides to withdraw, we will carry out follow-ups to confirm the well-being of participants.

Potential side effects

As mentioned previously, anecdotal reports have reported that as a consequence of taking the Lightning Stiks, individuals may suffered from headaches in the first few days of taking them. However, this could potentially be minimized by taking only half a Stik initially, and increasing the dose over 2 days. Further, the doses of the ingredients are much lower than those found in capsules and well below the RDA - as such, no ingredient is given in a medicinal dose. Because the doses are all below RDA, safety issues for any of the proposed ingredients are very unlikely. Further, all doses are well below the Tolerable Upper Intake Limit (UL), which is considered the highest amount of daily nutrient intake that is not likely to cause any adverse effects (Nutritional Institutes of Health, n.d.). This low risk of adverse effects was supported by the findings of the STAR trial (not published), showing that only a small number of side effects were present in the study (drowsiness and reduced appetite), and these were temporary and disappeared during the duration of the trial.

Further, in an RCT conducted at the University of Canterbury with adults (Rucklidge et al, 2014), the only recurring side effect of the formula was the aforementioned transitory gastrointestinal difficulties (loose stool, nausea or vomiting, if the product was taken on an empty stomach, contrary to recommendation) although this side effect did not occur more frequently in the active group as compared with the placebo group. It is important to note that this side effect typically lasts only a few days and can be addressed by staying hydrated. In addition, there have been 34 studies to date on the EMP micronutrient formula showing that no serious side effects or other effects have been noted. A recent safety study has been published documenting its safety and tolerability: Rucklidge, J., Eggleston, M. J., Ealam, B., Beaglehole, B., & Mulder, R. T. (2019). An observational preliminary study on the safety of long-term consumption of micronutrients for the treatment of psychiatric symptoms. *The Journal of Alternative and Complementary Medicine*, *25*(6), 613-622.

Cultural sensitivity

We have consulted with the Māori Research Advisory Group at the University of Canterbury regarding this type of research and the study has received approval to conduct nutritional research with Māori. The Ngai Tahu Consultation and Engagement Group (NTCEG) was consulted on 22/07/2021 by means of the Māori Consultation form and they have approved the study process on 30/07/2021. No issues were identified, and further consultation with Māori is not required. The group is available for further consultation throughout the project.

Within Te Puna Toiora and in the proposed research project, providing a holistic approach to mental health is the highest priority, aiming to begin to address the inequity in health outcomes between Māori and non-Māori by being culturally responsive. In the proposed research project, members of all ethnicities are invited to participate, with an emphasis on increasing Māori participation. Specifically, Māori service providers will be approached in order to reach Māori whānau. Further, measures will be put in place to ensure that Māori customs and traditions will be respected, such as having a cultural advisor available to provide extra support if needed. We also consulted the cultural advisor on the design of our previous projects and the design of this one is modelled on that of others that have received her input. In addition, this research aligns with the Māori health model Te Whare Tapa Whā as the role of kai in wellbeing has long been understood by Māori. Focusing on nutrition to improve mental health takes steps in upholding mātaranga Māori. Indeed, three of the four cornerstones of Te Whare Tapa Whā are represented within this research; taha tinana (physical health), taha hinengaro (mental health), and taha whānau (family health). Further, over the last year, the Mental Health and Nutrition Research lab, Te Puna Toiora, has been focusing on increasing Te Reo used within the lab, which is reflected in being gifted a Māori name, translating words within the lab into Māori, and having bilingual business cards. We will ensure that Te Reo is used within the information sheet as well to ensure that the research is perceived as welcoming for Māori. Finally, participants have the option to discuss with the research team any queries or worries that they may have at any time. These options will be clearly communicated via the information sheet, which individuals are advised to read before commencing participation.

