### Assessment Tools

An on-line survey created with Qualtrics will ask the participants and their parents to complete measures of emotion dysregulation, irritability, inattention, hyperactivity/impulsivity, diet, sleep, depression, anxiety and stress. The measures that are proposed in this study are standard measures used in clinical trials. In addition, the study coordinator will meet with the participants once a month in person at Te Puna Toiora to collect data on emotion dysregulation, mood, side effects, and interpersonal skills. If participants cannot be met in person, these meetings will be held via Zoom or other online platforms.

Primary outcome measures

*Clinician-administered:*

*The Clinician Affective Reactivity Index (Parent/Child Interview Guide) (CL-ARI):* This scale is a parent-report measure that assesses emotion regulation and irritability in children over the past week, looking at temper outbursts and irritable mood, and their frequency, severity, and duration. Further, it assesses whether the child’s irritable behaviour causes problems in the family, impairments in school, and assesses potential improvements over time. The CL-ARI has good internal consistency (*α* = .89) and adequate test-retest reliability (*ICC* = .67) (Haller et al., 2020). In the proposed study, the study coordinator will meet the parent and the child every four weeks to collect data on the CL-ARI in person.

*Clinical Global Impressions - Improvement Scale (CGI-I) (Guy, 1976):* The CGI-I is a clinician-administered scale that rates, based on all information obtained from all raters (parents, child and significant other) how much better/worse the participant is functioning since baseline across irritability/emotion dysregulation, mood, stress, energy, and sleep. Each item has seven responses, ranging from “very much improved” (1) to “very much worse” (7) and helps to provide a brief, overall assessment of the participant. The CGI-I is not used during baseline assessment. The CGI-I has demonstrated high external validity (*r* = 0.74) (Kadouri et al., 2007) and is widely used in clinical trials.

Secondary outcome measures

*Clinician-administered:*

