*Clinical Global Impressions – Severity Scale (CGI-S) (Guy, 1976)* is a clinician-rated evaluation of symptom severity by means of the question: “Considering your total clinical experience with this particular population, how impaired is the patient at this time?” The item is scored on a 7-point Likert scale, ranging from 1 (normal, not impaired) to 7 (markedly impaired) (Busner, 2007). The CGI-S is commonly used in clinical trials and has shown to be sensitive to clinical change in diagnostically diverse populations. In the proposed study, it is administered during the baseline assessment and at the end of the study, giving an overall impression of the participants’ functioning before and after the intervention.

*Parent- or other-adult administered:*

*Affective Reactivity Index (ARI) (Parent version)* (Stringaris et al., 2012): The ARI is a concise, parent-rated scale assessing the child’s irritability. It incorporates seven items that ask about feelings of irritability during the past seven days (e.g., “My child is easily annoyed by others”, “My child gets angry frequently”, “Overall, irritability causes my child problems”). How true a statement is can be scored on a 0 (not true) to 2 (certainly true) Likert scale. It has been shown to have good internal consistency (*α* = .84 - .92) (Ezpeleta et al., 2020) and is considered an appropriate measure to assess irritability (Stringaris et al., 2012).

*Strengths and Difficulties Questionnaire (SDQ)* (Goodman, 1997): The Strength and Difficulties Questionnaire consists of 25 items across five subscales, measuring emotional symptoms, conduct problems, hyperactivity/inattention, peer relationship problems, and prosocial behavior in 4-17 year old children and adolescents (Stone, Otten, Engels, Vermulst, & Janssens, 2010). Each item is scored on a 3-point Likert scale (‘not true’, ‘somewhat true’, and ‘certainly true’) by the child’s parents. Scores between 0-13 are considered normal, whereas scores between 17-40 represent severe psychological symptoms.

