## Statistical Analysis

***Exploratory analysis***

Before the data will be further analysed, all data sets will be cleaned. The demographic data of the participants will be presented in a table, describing gender, age, education, and medical history of each participant. For each variable at each time point group data in the form of the range, median, mean, and standard deviation will be tabulated, frequency distributions plotted and examined, and missing or anomalous data points investigated. Missing data will be handled following the ‘last observation carried forward’ method. Correlations between measures within and across time points will be examined to assess consistency (within time) and predictability (across time and measures) of responding.

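### Unrestricted LOCF in an ON/OFF withdrawal design gives some early leavers CL-ARI scores from the opposite condition, and no outcome assessment at discontinuation is specified to limit the loss

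*Protocol*

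**What the plan says.** - **Missing data.** Protocol, Exploratory analysis: missing data are handled by "last observation carried forward". No phase or condition limit is attached. The Nomothetic analysis section plans group analyses "which will involve hierarchical linear modeling" and does not say whether these use filled or observed scores.
- **Primary outcome timing.** Protocol, Assessment Tools: "the study coordinator will meet the parent and the child every four weeks to collect data on the CL-ARI in person". Appendix B shows one CL-ARI in each of phases 2 and 3, at week 4, and has no column for early termination.
- **Removal.** Protocol, Safety protocol related to visits at the University Lab: "If a protocol exclusion violation has occurred (i.e., participant requires psychiatric medications), the participant’s involvement will be discontinued". On clinically significant worsening or harm, the team "may decide that they should discontinue their participation in the trial". For anyone discontinued or withdrawing, "we will carry out follow-ups to confirm the well-being of participants". No outcome measure is named for that contact.
- **Measures with few time points.** The CGI-S: "it is administered during the baseline assessment and at the end of the study". The AARP is given once, at the end of the trial (Assessment Tools; Appendix B). For the other primary measure: "The CGI-I is not used during baseline assessment".

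**The concern.** Hypotheses 2 to 5 rest on comparing ON with OFF, within children and between groups. Early in the trial the condition changes every four weeks, and the CL-ARI is taken once in that time. If a child leaves between a switch and the next CL-ARI, the last available score belongs to the condition just ended, and LOCF enters it as if it came from the new one. Carrying it further can cross more switches.

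Removal is also partly tied to the outcome. A child taken out because of worsening, or because medication is needed, is not a random loss, and any change since the last visit may never reach the CL-ARI. The AARP, which informs acceptability (Hypothesis 1) and satisfaction (Hypothesis 8), has no earlier value to carry. The CGI-S has only its baseline value, so under LOCF a leaver with no final rating has a change of exactly zero.

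**Working it through.** The protocol gives no figure for attrition or its effect, so there is nothing of its own to reproduce. The check counts cells from the schedule.

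**Inputs.** Conditions and phase lengths come from Study design, and the CL-ARI frequency from Assessment Tools. Baseline counts as OFF. The timeline agrees with Hypothesis 6, which expects eight weeks with both groups ON (weeks 12 to 20).

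- Group 1 CL-ARI: week 0 OFF, 4 ON, 8 OFF, 12, 16 and 20 ON.
- Group 2 CL-ARI: week 0 OFF, 4 OFF, 8 ON, 12 OFF, 16, 20 and 24 ON.

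**Mismatched cells out of carried cells, one child leaving per interval**

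| Leaves in weeks | G1, LOCF as written | G1, plus CL-ARI at exit | G2, LOCF as written | G2, plus CL-ARI at exit |
|---|---|---|---|---|
| 0–4 | 4/5 | 1/5 | 4/6 | 4/6 |
| 4–8 | 1/4 | 3/4 | 4/5 | 1/5 |
| 8–12 | 3/3 | 0/3 | 1/4 | 3/4 |
| 12–16 | 0/2 | 0/2 | 3/3 | 0/3 |
| 16–20 | 0/1 | 0/1 | 0/2 | 0/2 |
| 20–24 | – | – | 0/1 | 0/1 |
| Total | 8/15 | 4/15 | 12/21 | 8/21 |

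Example: a group 1 child leaving in weeks 0–4 carries baseline OFF to weeks 4, 8, 12, 16 and 20. Only week 8 is OFF, so 4 of 5 are mismatched.

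An exit CL-ARI with LOCF unchanged lowers the totals but raises mismatch in one interval per group, from 1/4 to 3/4 (group 1 weeks 4–8, group 2 weeks 8–12). If scores may not cross a switch, the count is 0 in both groups, with or without an exit visit.

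**Exposed time for the next score.** CL-ARI: group 1 weeks 0–12, or 12 of 20; group 2 weeks 4–16, or 12 of 24. For the ARI every two weeks: group 1 weeks 0–2, 4–6 and 8–10, or 6 of 20; group 2 weeks 4–6, 8–10 and 12–14, or 6 of 24.

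**Possible size for the CL-ARI (removal rate and change are assumed).** The error in a phase mean is k × c / 20, with k children removed of 20 and an unrecorded change of c SD.

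- k = 1, c = 0.5: 1 × 0.5 / 20 = 0.025 SD.
- k = 3, c = 1.0: 3 × 1.0 / 20 = 0.15 SD.
- Change already recorded: 0.

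For scale, the standard error of a 20-child mean is 1/√20 = 0.22 SD.

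**Direction.** Unrecorded worsening while ON leaves the ON mean too favourable and flatters the product. While OFF it leaves the OFF mean too favourable and works against the product. If instead leaving were unrelated to response and a share m of each group left during weeks 4–8, the week 8 contrast would shrink to (1 − 2m) of its true size, because both groups have just switched: 0.90 for 1 of 20 per group, 0.80 for 2 of 20. This takes the effect as fully present when ON and fully absent when OFF.

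**AARP (assumed).** The total runs from 8 × 1 = 8 to 8 × 6 = 48. If D of 40 families leave and would score w points lower, the completer mean is too high by D × w / 40: 2 × 5 / 40 = 0.25 to 8 × 15 / 40 = 3.0 points, or 0 if leavers would score the same.

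**The case against.** The strongest reply is that the safety section is merely silent. It does not say that questionnaires stop, its well-being follow-up suits its purpose, and a withdrawal procedure could stand in pages that are not public. This is right, and a reader who infers that outcome collection ends at discontinuation goes further than the text. The point therefore rests first on the LOCF rule, which is stated, and only second on the missing exit assessment. It also follows that AARP and CGI-S loss among leavers is probable, not certain.

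Second, worsening that leads to removal must first be noticed, often through a two-weekly questionnaire or a monthly visit, so it may already be recorded. This stands as well: the error is then zero. The two-weekly ARI and CGI-I are less exposed, though the CGI-I has no baseline score to carry, and neither replaces the CL-ARI.

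Third, LOCF appears under Exploratory analysis, in an open-label exploratory study that leans on visual single-case analysis, and nothing says that filled scores enter the hierarchical model. That is fair. However, the section opens with steps taken before further analysis and makes no exception for later ones. A SAP could restrict the rule; it could not supply a CL-ARI or AARP that was never taken.

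Fourth, even the worst assumed case, 0.15 SD, is below one standard error of a 20-child mean. This limits the point but does not remove it, since the error is systematic and avoidable.

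**Conclusion.** The point holds as a flaw in the missing-data rule for this design, with a weaker companion point about data collection. Followed as written, LOCF puts opposite-condition scores into the comparisons behind Hypotheses 2 to 5 whenever a child leaves between a switch and the next CL-ARI.

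Three stronger readings are not supported:

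- That about half of all carried scores will be wrong. The 8 of 15 and 12 of 21 assume one departure in each interval and are not forecasts. Departures in the final ON phase after its first visit cause no mismatch.
- That LOCF favours the product. For the CL-ARI the direction is unknown and the effect may be zero. Only the AARP has a likely direction, upward, and that assumes leavers are less satisfied and are not asked.
- That an exit visit alone cures the problem. It leaves 4 of 15 and 8 of 21 cells mismatched. In addition, the CL-ARI covers the past week, so a score taken within a week of a switch mixes conditions.

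All sizes beyond the cell counts rest on assumed removal rates and changes.

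**What to change.** **Main change (Exploratory analysis).** State that no score is carried across an ON/OFF switch, and that the planned hierarchical linear model uses observed scores. This costs a sentence or two.

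**Supporting change (Safety protocol).** Separate stopping the product from stopping assessment. Where the family agrees, take CL-ARI, CGI-I, CGI-S, ARI and AARP at discontinuation, before any psychiatric medication starts where possible, using the online, Zoom or follow-up contact already planned. Record the number of days since the last switch. The cost is one extra, refusable set of questionnaires for a few families, and some will decline.

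**Reporting.** Give AARP results with the number missing among all children who started the product.

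Do not adopt the supporting change while leaving LOCF as it is.
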